**3.12.2 Questionnaire**

The questionnaire will be pre-tested and assisted self-administered questionnaire in English language as in Appendix. The questionnaire will be divided into ten sections namely, socio demography, dietary intake, smoking, alcohol consumption, physical activity, CVD knowledge, motivation, behavioral skills, BMI (weight and height), and blood pressure (diastolic and systolic). The questionnaires will be administered in a classroom setting in all the selected schools.

Section one of the questionnaire will be used to access students’ age, gender, grade, ethnicity, monthly pocket money, and family history. Data on age will be collected in the form of open ended question and students will fill in the blank space provided. The rest (ethnicity, gender, religion, and family history) are in the form of closed ended questions and students are to choose the answers that will pertained to them.

Section two is a seven-day dietary recall instrument which are foods items mostly consumed in Ghana, the Ghana Demographic and Health Survey, (GDHS), (GSS, 2009; Nti, 2008) to assess dietary consumption. Amounts of each food intake will be stated with the use of handy measure tables (food weights). This are based on the weights of foods with their equivalent handy measure tables which are commonly used

in Ghana (Owusu, Ankrah, Boateng, & Anteh, 1995). Then frequency of consumption of certain foods will be scored based on one (1) for never dietary consumption, two (2) for 2-3 times per week, three (3) for 4-5 times per week, four (4) for 6 times per week, and five (5) for daily intake of a particular food item.

Section three and four are the modified smoking and alcohol questionnaires, Global Youth Tobacco Survey (GYTS) developed by WHO and Centre for Disease Control and Prevention (CDC) (CDC, 2008). It is a school-based adolescents’ self- administered questionnaire which comprised of a set of core questions that will be used to evaluate tobacco and alcohol control and prevention programmes among secondary school students. Students would be classified as never, ever, and current smokers and alcohol consumption. Strict confidentiality will be ensured among researchers to avoid disclosure of smoking and alcohol statuses to school authorities, teachers, or parents.

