**3.15.2 Dependent Variables**

The dependent variables of this study are sub divided into primary and secondary outcomes. There were;

i. The primary outcomes are CVD knowledge and its risk factors, motivation, behavioral skills, physical activity, smoking, alcohol consumption, and dietary intake.

ii. The secondary outcomes are body weight, BMI, diastolic and systolic blood pressures.

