**3.16.6 Diet Practices**

This referred to the total frequency in scores and amount of diet for each food item. Consumption of foods such as fruits, vegetables, seafood, and water were considered as healthy foods while the consumption of foods such as fried foods, fried eggs, fried chicken, fats and oils, plain sugar, sweet snacks, salted fish, and carbonated drinks are considered as unhealthy foods.

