**SECTION 2 : DIET ASSESSMENT**

This refers to your diet over the past 7 days (one week). Please write the number of each food item consumed and circle the corresponding frequency of consumption

| **18. Fruits &**  **Vegetables** | **Handy measure** | **Number**  **consumed** | **(1) Never** | **(2) 2-3**  **Times per week** | **(3) 4-5**  **Times per week** | **(4) 6 Times**  **per week** | **(5) Daily** |
| --- | --- | --- | --- | --- | --- | --- | --- |
| Banana | 3 Middle finger Size |  | 1 | 2 | 3 | 4 | 5 |
| Mango | Orange average size |  | 1 | 2 | 3 | 4 | 5 |
| Pawpaw | Empty sardine tin size |  | 1 | 2 | 3 | 4 | 5 |
| Pineapple | Empty sardine tin size |  | 1 | 2 | 3 | 4 | 5 |
| Orange | Orange average size |  | 1 | 2 | 3 | 4 | 5 |
| Pear | Large orange size |  | 1 | 2 | 3 | 4 | 5 |
| Tangerine | Empty milk tin size |  | 1 | 2 | 3 | 4 | 5 |
| Watermelon | Empty sardine tin size |  | 1 | 2 | 3 | 4 | 5 |
| Cabbage | Stewing spoon level |  | 1 | 2 | 3 | 4 | 5 |
| Carrots | Stewing spoon level |  | 1 | 2 | 3 | 4 | 5 |
| Cassava  leaves | Stewing spoon level |  | 1 | 2 | 3 | 4 | 5 |
| Kontomire  (green leafy vegetable) | Stewing spoon level |  | 1 | 2 | 3 | 4 | 5 |
| Cucumber | Empty small tomato tin  size |  | 1 | 2 | 3 | 4 | 5 |
| Okro/okra | Stewing spoon level |  | 1 | 2 | 3 | 4 | 5 |
| Onions | Table spoon/big spoon  level |  | 1 | 2 | 3 | 4 | 5 |

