**SDS3**

| Fruit juice | 250 mls pack size | |  | 1 | 2 | 3 | 4 | | 5 |
| --- | --- | --- | --- | --- | --- | --- | --- | --- | --- |
| Malt drink | 330 mls bottle size | |  | 1 | 2 | 3 | 4 | | 5 |
| Minerals | 300 mls bottle size | |  | 1 | 2 | 3 | 4 | | 5 |
| (coke, fanta, |  |  |  |  |  |  |  |  |  |
| sprite, etc) |  |  |  |  |  |  |  |  |  |
| Toffees | 1 average toffee size | |  | 1 | 2 | 3 | 4 | | 5 |
| Sugar (you | Teaspoon size | |  | 1 | 2 | 3 | 4 | | 5 |
| add to food) |  |  |  |  |  |  |  |  |  |
| **25. Snacks** | **Handy measure** | | **Number** | **(1) Never** | **(2) 2-3** | **(3) 4-5** | **(4) 6 Times** | | **(5) Daily** |
|  |  |  | **consumed** |  | **Times** | **Times** | **per week** | |  |
|  |  |  |  |  | **per week** | **per week** |  | |  |
| Biscuit | **1 biscuit** | **(cream** |  | **1** | **2** | **3** | **4** | | **5** |
|  | **crackers size)** |  |  |  |  |  |  |  |  |
| Cakes | Orange size | |  | 1 | 2 | 3 | 4 | | 5 |
| Chips | Empty sardine tin size | |  | 1 | 2 | 3 | 4 | | 5 |
| Doughnuts | Large egg size | |  | 1 | 2 | 3 | 4 | | 5 |
| Fried chicken | Match box size | |  | 1 | 2 | 3 | 4 | | 5 |
| Fried egg | Standard egg size | |  | 1 | 2 | 3 | 4 | | 5 |
| Ice cream | Empty small tomato tin  size | |  | 1 | 2 | 3 | 4 | | 5 |
| Meat/sausage | Empty small tomato tin  size | |  | 1 | 2 | 3 | 4 | | 5 |
| khebab |  |  |  |  |  |  |  |  |  |
| Popcorn | Empty milk tin size | |  | 1 | 2 | 3 | 4 | | 5 |
|  |  |  |  |  |  |  |  |  |  |
| **26. Water** | **Handy measure** | | **Number** | **(1)** | **(2) 1 per** | **(3) 2-3** | **(4)** | **4-5** | **(5) 6 or** |
| **consumption** |  |  | **consumed** | **Rarely** | **day** | **Times** | **Times** | **per** | **more times** |
|  |  |  |  |  |  | **per day** | **day** |  | **per day** |
| Water (daily) | 500 mls (sachet water) | |  | 1 | 2 | 3 | 4 | | 5 |

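### The seven-day diet frequency scale has no category for a food eaten once in the week, which leaves a hole in the frequency component of a primary outcome

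*Protocol*

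**What the plan says.** Section 3.12.2 describes the diet section of the questionnaire as a weekly recall: "Section two is a seven-day dietary recall instrument". Each food's frequency is "scored based on one (1) for never dietary consumption, two (2) for 2-3 times per week, three (3) for 4-5 times per week", then "four (4) for 6 times per week, and five (5) for daily intake of a particular food item".

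The form in Appendix A, Section 2, has the same recall window and the same five column headings over each of its eight food tables, items 18 to 25. Its instruction to the student is: "Please write the number of each food item consumed and circle the corresponding frequency of consumption". None of these tables offers once, rarely or other.

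Section 3.15.2 lists dietary intake among the primary outcomes: "behavioral skills, physical activity, smoking, alcohol consumption, and dietary intake". Section 3.16.6 gives its operational definition: "This referred to the total frequency in scores and amount of diet for each food item". Section 3.17.3 analyses dietary intake with t-tests and a mixed-design repeated measures ANOVA. It then replaces missing values by multiple imputation and fits a generalized linear mixed model.

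**The concern.** A set of response categories should give every possible answer exactly one code. This scale goes straight from never to two or three times a week. The food lists name individual items such as mango, pawpaw, doughnuts, fried chicken and salted fish, and once in the past week is an ordinary answer for such items.

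A student in that position has three choices: understate, overstate, or leave the row blank. Two students with the same intake can therefore differ by one score point on a row, and one student can answer differently at baseline and at six months with no change in diet. Small real changes at the low end of the scale, from none to one or from two to one, have no faithful record in the frequency score.

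A blank is not a neutral outcome either. It would be imputed from a scale on which none of the available codes is correct for that student. The answer was never collected, so no later analysis can recover it.

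**Working it through.** The plan states no figure for this point, so there is none to reproduce. Three checks apply.

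**1. Is the scale exhaustive?** Inputs: the codes in 3.12.2 and the column headings of Appendix A items 18 to 25, which agree. Reading daily as seven times in the week:

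| Times eaten in 7 days | Code |
|---|---|
| 0 | 1 |
| 1 | none |
| 2, 3 | 2 |
| 4, 5 | 3 |
| 6 | 4 |
| 7 | 5 |

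Seven of the eight counts have a code; the count of one does not. The prose rule and the printed tables carry the same categories, so damage to the tables during text extraction does not explain the gap.

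**2. How many rows share the gap?** Counting the variable labels in Appendix A: fruits and vegetables 17, tubers and plantain 6, cereals and grains 7, legumes 7, animal products 9, fats and oils 8, soft drinks and sweets 7, snacks 9.

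17 + 6 + 7 + 7 + 9 + 8 + 7 + 9 = 70.

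Water (item 26) is not in this count. It has its own daily scale, which includes once per day.

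**3. Do other scales in the form cover a single occasion?** Yes. The alcohol table (item 50) has a column for once a week. The spare-time activity list (item 56) has 1-2 times. The after-school and evening activity items (59 and 60) each have a category for one time in the last week. Only the food frequency scale omits it.

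**Illustration of possible size.** The documents give no distribution of intake. Assume, for illustration only, that the number of days on which a food is eaten follows Binomial(7, p). The share of answers at exactly one is then 7 × p × (1 − p)^6:

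| Assumed p | Share at exactly one |
|---|---|
| 0.05 | 26% |
| 0.10 | 37% |
| 0.15 | 40% |
| 0.20 | 37% |
| 0.30 | 25% |
| 0.50 | 5% |

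The share is large for foods eaten seldom and small for staples. This shows only that the missing category need not be rare. It does not estimate the share in this trial.

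**The case against.** The strongest reply is that frequency is only half of the outcome. Section 3.16.6 combines the frequency score with the amount, and the form asks for the number consumed before the frequency is circled. A student who ate one portion can write that down, so the information is not wholly lost. This stands as mitigation. But the column counts handy measures, not occasions. It supplies no frequency code, and the frequency score stays wrong or missing.

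A second reply is that the reach is narrower than 70 rows. Section 3.12.2 speaks of scoring certain foods, and hypotheses 6 and 7 and Section 3.16.6 name particular ones. Legumes (7 rows), milk, milk powder, red meat and snail are not among them, which is at least 11 rows. A reader might infer that all 70 rows drive the tests of the primary outcome. The documents show only that all 70 rows are printed with the gap.

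A third reply is that the plan already has safeguards: a pre-test, assisted completion, face validation in 50 students, and expert content validation. Any of these might catch the omission. None states a rule for a food eaten once, and face validation asks about question order, clarity and appropriateness rather than completeness of the categories.

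A reader might also infer that the gap favours the intervention, because taught students could round fruit up and fried food down. The documents do not support that as a finding. Both arms receive the same questionnaire at both times, so the gap itself is identical across arms. Answers shaded by teaching are a possible risk of unblinded self-report, and neither their direction nor their size can be derived from the documents.

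**Conclusion.** The defect is certain and narrow. The frequency scale omits one of the eight weekly counts on all 70 food rows, so an answer of once is either misclassified or left blank and imputed. It touches the frequency component of one of the primary outcomes; the amount component softens the effect without closing the gap.

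The size is unknown. The binomial shares of 5% to 40% rest wholly on assumed values of p. At the least, one should expect added noise at the low end of the scale. It would go too far to say that changes in low intake cannot be measured at all, or that the comparison between arms is biased.

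This is a response rule that cannot be followed for a plausible answer. It is not a detail that could be left to a statistical analysis plan, because the form itself fixes what is recorded.

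**What to change.** Before baseline, insert a separate category for once per week, as the alcohol table already has, in 3.12.2 and in every food table of Appendix A, items 18 to 25. Renumber the score, for example 1 = never, 2 = once, 3 = two or three times, 4 = four or five times, 5 = six times, 6 = daily. Every count from 0 to 7 then has exactly one code. The planned pre-test can check that students use the new category.

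A minimal fallback is to relabel code 2 as 1-3 times per week. That makes the scale exhaustive and keeps the 1-5 scoring, but a change between once and two or three times would still register as no change.

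The cost is small: the table headings, the 1-5 scoring text and the data-entry codes change. The protocol already plans to give the same questionnaire at follow-up, so nothing needs adding there. For that reason the change has to precede baseline: altering the scale between the two rounds would make the scores non-comparable.

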**1.6 Research Hypotheses**

The research hypotheses of this study are:

1. There will be no difference in the socio-demographic characteristics between the intervention and control groups at baseline.

2. The behavioral modification intervention program will be effective in improving the knowledge of CVD and its risk factors, motivation, and behavioral skill score among the participants in the intervention group as compared to control group and also within the groups from baseline to six months among secondary school students in Brong Ahafo, Ghana.

3. The behavioral modification intervention program will be effective in promoting physical activity levels of participants in the intervention group as compared to control group and also within the groups from baseline to six months among secondary school students in Brong Ahafo, Ghana.

4. The behavioral modification intervention program will be effective in reducing the prevalence of smoking among participants in the intervention group as compared to control group and also within the groups from baseline to six months among secondary school students in Brong Ahafo, Ghana.

5. The behavioral modification intervention program will be effective in reducing the prevalence of alcohol consumption of participants in the intervention group as compared to control group and also within the groups from baseline to six months among secondary school students in Brong Ahafo, Ghana.

6. The behavioral modification intervention program will be effective in promoting fruits and vegetable intake among participants in the intervention group as compared to control group and also within the groups from baseline to six months among secondary school students in Brong Ahafo, Ghana.

7. The behavioral modification intervention program will be effective in increasing seafood and water intake and reducing carbohydrates, fats and oils, fried eggs, fried chicken, carbonated drinks, plain sugar, sweet snack, and salted fish intake among participants in the intervention group compared to control group and also within the groups from baseline to six months among secondary school students in Brong Ahafo, Ghana.

8. The behavioral modification intervention program will be effective in reducing body weight and BMI of participants in the intervention group as compared to control group and also within the groups from baseline to six months among secondary school students in Brong Ahafo, Ghana.

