**2.6.4 Unhealthy Diet**

There is an association between dietary habits and cardiovascular risk factors such as overweight, obesity, diabetes, serum cholesterol, and blood pressure (Verschuren,

2012). Childhood obesity is a risk factor of CVD in adulthood, metabolic syndrome and development of arteriosclerosis. Cardiovascular risk factors and obesity affects vascular structure and function, and increased arterial stiffness (Herouvi, Karanasios, Karayianni, & Karavanaki 2013). Eating behaviors are central because the youth’s physical development, health, and identity are determined by factors such as knowledge, attitudes, sociodemographic characteristics, behavioral, and lifestyle factors and that behavioral patterns formed in adolescents are likely to influence long term behaviors (Abraham, Noriega, & Shin, 2018; Scaglioni et al., 2018; Sultana,

2017).

A study among adolescents reported high intake of sweet snacks and soft drinks while the consumption of fruits, vegetables, and fish was low (Gebremariam, Henjum, Terragni, & Torheim, 2016). A review among adolescents on dietary intake and sedentary behavior also found high consumption of fried foods including energy dense snacks and beverages with lower consumption of fruits and vegetables (Pearson & Biddle, 2011). In a study by Zaborskis et al. (2012) reported of high intake of sugar, carbonated drinks, pastries, chips and fast foods among school-aged adolescents. In another study, 33.8% of the students indicated they preferred carbonated drinks for snack (Buxton, 2014). Further, another study reported that consumption of fried and sugary foods among students were high (Alangea, Aryeetey, Gray, Laar, & Adamu,

2018). In a study on dietary salt intake reported that consumption of salt among participants was high (Menyanu et al., 2017). Furthermore, water intake among Ghanaian youth is inadequate (Doegah & Amoateng, 2018). Ministry of Health, Ghana (MOH, 2012) has indicted that adolescents have been consuming unhealthy foods that could lead to the onset of diseases during adulthood. This is because most students do not have knowledge on food and nutrition and are not aware of the repercussions of consuming unhealthy diets.

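### The diet frequency code stops at daily, so it cannot see change in a single food that stays at or above once a day, and the form does not say whether the amount column makes up for this

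*Protocol*

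**What the plan says.** Protocol 3.12.2 sets one frequency scale for foods. It starts at "one (1) for never dietary consumption, two (2) for 2-3 times per week" and continues with "three (3) for 4-5 times per week, four (4) for 6 times per week, and five (5) for daily intake of a particular food item". Appendix A, Section 2 prints this scale against every food in items 18 to 25. Water (item 26) has a scale of its own that counts times per day, from rarely up to six or more.

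Frequency is not the only diet measure. Section 3.12.2 also has amounts stated in handy measures, and each row of the form has an open 'Number consumed' column. Section 3.16.6 defines diet practices by both: "This referred to the total frequency in scores and amount of diet for each food item".

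Section 3.15.2 lists dietary intake among the primary outcomes. In section 1.6, hypothesis 6 expects fruit and vegetables to rise, and hypothesis 7 includes "reducing carbohydrates, fats and oils, fried eggs, fried chicken, carbonated drinks, plain sugar, sweet snack, and salted fish intake".

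**The concern.** Several of the listed foods can plausibly be eaten at more than one meal a day: cooking oils, added sugar, starchy staples, and the onions, pepper and tomatoes that sit in the vegetable block. The scale separates 4-5, 6 and 7 occasions a week but nothing from 7 upward. If some students start above once a day, the code has a ceiling in a range where the programme is meant to act.

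At stake is the frequency component of a primary outcome. True change above the ceiling is recorded as zero, which pulls that component towards no difference between arms. If the amount column is filled in per occasion, the change is missing from both measures and cannot be recovered after data collection.

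**Working it through.** The plan gives no figure to reproduce here, so the check applies the 3.12.2 scale to simple cases.

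**Rows affected.** Counting items 18 to 25 in Appendix A: 17 + 6 + 7 + 7 + 9 + 8 + 7 + 9 = 70. Water is excluded because its scale differs.

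**Coding.** With t the occasions per week for one item: t = 0 gives 1; 2-3 gives 2; 4-5 gives 3; 6 gives 4; 7 or more gives 5. (Once a week has no code. That is a separate gap and is not used below.)

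**Cases.** The amount columns assume one handy measure per occasion.

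| Occasions per week, one item | True change | Frequency code | Amount as 7-day total | Amount as daily total | Amount per occasion |
|---|---|---|---|---|---|
| 21 to 7 | (7 − 21)/21 = −67% | 5 to 5 | 21 to 7 | 3 to 1 | 1 to 1 |
| 14 to 7 | (7 − 14)/14 = −50% | 5 to 5 | 14 to 7 | 2 to 1 | 1 to 1 |
| 7 to 14 | (14 − 7)/7 = +100% | 5 to 5 | 7 to 14 | 1 to 2 | 1 to 1 |
| 21 to 6 | (6 − 21)/21 = −71% | 5 to 4 | 21 to 6 | falls | 1 to 1 |
| 21 to 3 | (3 − 21)/21 = −86% | 5 to 2 | 21 to 3 | falls | 1 to 1 |

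The first three cases are invisible to the code and the last two are not. In the first three, the amount column records the change on two of the three readings of what it holds.

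**Which reading applies.** Section 2 of the form is headed as a recall of the past seven days, which suggests a weekly total. Against that, the instruction pairs the number with a matching frequency, which can also be read as portion per occasion. Item 50 on alcohol uses the same construction with frequencies as low as once a month, where a weekly total fits poorly. Neither text settles the matter.

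**Different foods.** Fruit and vegetables occupy 17 separate rows. A student who eats an orange daily and adds a daily banana moves the banana row from 1 to 5. Only a second daily serving of the same item is lost.

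**Size.** For a food meant to fall, let q be the share of students above once a day at baseline, and r the share of those who cut down but stay at or above once a day. The share of students whose reduction the code misses is q × r. The Protocol gives neither. Purely as an assumption, q between 20% and 50% with r between 0 and 1 gives 0.20 × 0 = 0 up to 0.50 × 1 = 50%. That range is too wide to serve as an estimate.

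**The case against.** The strongest reply is that the outcome is not the frequency code alone. Section 3.16.6 defines it by frequency and amount, the amount field has no cap, and hypotheses 6 and 7 speak of intake. On a 7-day or daily total, every hidden case above is recorded. Which measure is analysed may be settled in a statistical analysis plan that is not at hand. This largely stands. A reader might infer that the diet outcome as a whole scores no change and that the trial's dietary effect is biased towards none. The documents do not support that. It would follow only if frequency is analysed alone or the number is entered per occasion.

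Two further inferences fail. One is that any doubling of fruit is lost; that holds only for the same fruit. The other is that the effect shrinks by the share of heavy consumers; that needs every one of them to stay at or above daily, and the share itself has no source. Section 2.6.4 cites a study in which "consumption of fried and sugary foods among students were high", but high does not mean more than once a day.

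What the reply does not remove: frequency is a stated component of the outcome and the part to which 3.12.2 gives numerical codes. It cannot see change above once a day, and whether the amount column compensates depends on a period the form leaves unstated.

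**Conclusion.** The point holds in a limited form. On 70 food rows the frequency component of dietary intake has a ceiling at once a day: a change of −67%, −50% or +100% in one item can score 5 to 5. Falls below daily register, and so does the addition of a different food. Whether the loss reaches the outcome as a whole depends on what 'Number consumed' means. It does not if the field is a weekly or daily total and amount is analysed; it does if the field is a portion per occasion or frequency is analysed alone. The number of students affected cannot be computed from the Protocol. This is a cheap improvement to the instrument, not a defect that invalidates the diet outcome.

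**What to change.** In section 3.12.2 and in items 18 to 25 of Appendix A, split the top category into 'once a day' (5) and 'two or more times a day' (6), or count times per day as the water row already does. Label the 'Number consumed' column as the total over the past 7 days, so that the amount measure also registers intake several times a day. Make both changes before the form is pre-tested, and use the same form at baseline and at six months, since a scale altered between visits would itself produce apparent change.

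The cost is one more column, one line of instruction and a slightly longer form. The two-category split still does not separate two from three times a day, so the relabelled amount column is needed as well.
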